#### Secondary outcome measures (quantitative part)

Transsectoral information exchange and care efficiency:

Care efficiency and the transsectoral information exchange are recorded using self-constructed items. The items were developed by a team of physicians, psychologists and healthcare researchers working in the field. At baseline, the following variables will be collected in the patient questionnaire: process of care (e.g. procedure for taking family history at the study centres) measured by five items, use of medical services measured by a set of five items, and exchange of information measured by a set of nine items. At *t*1 and *t*2, transsectoral information exchange and care efficiency will be measured with a set of 13 items and 24 items, respectively, using a Likert scale. The medical staff survey at the HBOC-centre collects the following variables: completeness of clinical data and recording of working hours and services at the HBOC-centre, measured by a set of items outlined below in Table 1.

Genetic Counseling Outcome Scale (GCOS) [19]:

Increases in patient empowerment over a 9-month period will be measured using the Genetic Counselling Outcome Scale (GCOS-24) at three time points (see Table 1). The 24-item GCOS-24 assesses patient empowerment in the context of genetic counselling and is derived based on the grounded theory model [28]. It covers decision-making control, cognitive control, behavioural control, emotion regulation, and hope. The scale has been psychometrically tested and has high internal consistency (Cronbach’s alpha = 0.87) and test–retest reliability (*r* = 0.86) [19]. As there is currently no German version, the GCOS-24 has been translated, adapted and validated [29] with respect to the needs of individuals with a family history of cancer risk before and after genetic testing. To ensure efficient data collection, ten items are scored on a 4-point Likert scale at each time point [29].

Short-Form-Health-Survey-12 [20–22]:

Health-related quality of life is measured using the Short-Form Health Survey (SF-12) (see Table 1), which is based on the original American version of the SF-36 [22]. The assessment follows the eight-dimensional structure of the SF-36, with four dimensions represented by single items in the SF-12: general health perception, pain, vitality, and social functioning. The SF-12 is a standardised, cross-disease measurement tool with normative data available for the German population [21]. The same twelve items are administered and scored identically at all three time points.

#### Additional variables

At baseline, the following covariates will be collected in the patients’ questionnaire: sociodemographic and clinical variables (e.g. diagnosis of cancer, type of cancer) as measured with a set of six items, risk perception as measured with the subjective risk perception based on Kendel et al. [23] (two items), decisional conflict as measured with the Decisional Conflict Scale (DCS) [24, 25] (four items), technical affinity as measured by the ATI Scale [27] (two items) and user behaviour in the intervention group as measured with a set of two items (see Table 1).

Covariates at t1 include risk perception and user behaviour (three items each). Covariates at t2 comprise clinical variables (two items), risk perception (two items), and user behaviour (six items). In addition, at t2 the items for the extent of regret about the decision to perform genetic testing were measured with the Decision Regret Scale (DRS) [26] (eight items) (see Table 1).

#### Secondary outcome measures (qualitative part)

In the qualitative part of the study, the following secondary outcomes and covariates are analysed in greater depth and from a content-analytical perspective using semi-structured interviews and observations:→ Transsectoral information exchange and care efficiency→ Patient empowerment→ Quality of life→ Decision-making behaviour→ Subjective risk perception→ Technical affinity→ User behaviour dVP_FAM (intervention condition)

### Participant timeline {13}

The study is divided into two phases:

**First phase: screening in the study centres to identify a family history of cancer** (see Fig. 1)

**Fig. 1 Fig1:**
[figure not shown]
Flowchart of the first study phase: screening in the study centres

i. Screening under intervention conditions (see Fig. 1)

After registering in one of the local study centres, the patient is informed about the “dVP_FAM” project by nurses and medical assistants and receives a flyer with additional information. For patients wishing to participate and to use the care platform for screening, medical assistants create a temporary account and generate a QR code for initial registration and access to the digital questionnaire. The patient scans the QR code to register on the healthcare platform using either a provided tablet or their own smartphone. After agreeing to the terms of use and privacy policy, the patient logs in to the care platform. Patients then complete the digital family history questionnaire and share her data with the physicians involved in their treatment. In the consultation room, the physician logs into the care platform using their medical account to view the results of the family history from the digital questionnaire. The physician then evaluates the information about the patient’s family history and informs her about the result.

If the patient meets the inclusion criteria for a familial risk of breast and/or ovarian cancer according to the digital questionnaire, the physician can recommend an appointment for specialised care and counselling at the HBOC-centre (Charité or UM Greifswald). In this case, the physician at the study centre activates an account in the care platform for the patient and provides her with a unique password for registration. The patient may then use the platform at home to access plain-language content on familial breast and ovarian cancer on the care platform and to schedule an appointment for counselling at the HBOC-centre at Charité or UM Greifswald.

ii. Screening under control conditions (see Fig. 1)

Study centres under control condition conduct the survey of familial breast and ovarian cancer according to evidence-based guidelines as usual and without the digital platform. If, based on their family history, a patient shows a familial risk of breast and/or ovarian cancer, they can recommend a referral for counselling at a HBOC-centre (Charité or UM Greifswald). The appointment with the respective HBOC-centre follows the standard pathway (by telephone or e-mail). The reference “EK +/dVP_FAM” must be noted on the referral form so that a patient from a participating study centre can be clearly identified at the HBOC-centre to measure the primary endpoint and further inclusion in the longitudinal study.

**Second phase: recruitment at the HBOC-centres** (see Fig. 2)

**Fig. 2 Fig2:**
[figure not shown]
Flowchart of the second study phase: recruitment at the HBOC-centres

All patients attending the HBOC-centre referred by a study centre under intervention or control conditions are monitored. Patients with familial cancer risk according to the DKG-checklist are included in the analysis of the primary endpoint.

i. Recruitment for the longitudinal questionnaire study (see Fig. 2)

Patients who present at the specialised HBOC-centre after screening and agree to participate in the study complete a self-report questionnaire at three measurement points (*t*0: baseline; *t*1: 3 months; *t*2: 9 months). The baseline measurement t0 takes place after the initial counselling with a specialised physician in the HBOC-centre. Study participants receive an e-mail link to the online questionnaire after the counselling. Three and 9 months after the initial counselling, the study participants receive further online questionnaires for *t*1 and *t*2 via e-mail.

ii. Survey of medical staff at the HBOC-centre (see Fig. 2)

At the HBOC-centre, medical staff record all services performed before and after counselling on an individual patient basis using a self-report questionnaire. This allows to compare the efficiency of care under intervention and control conditions from a provider’s perspective.

iii. Qualitative study (interviews and observations) (see Fig. 2)**Interviews**To assess improvements of information exchange between providers, care efficiency, patient empowerment, and quality of life, semi-structured interviews are conducted with participating physicians (*N* = 24), nurses, and medical assistants (*N* = 24), and patients (*N* = 24) at two timepoints (first wave: baseline after study start; second wave: 5–7 months after study start).Interviews in study centres (physicians and nurses/medical assistants): Study centres under intervention conditions are informed about the interviews during their introduction to the dVP_FAM, while control centres receive this information via phone or e-mail. The second interview occurs 5 to 7 months after the first.Interviews with patients: The first patient interview takes place immediately after the initial counselling session at the HBOC–centre. Study staff ask patients if they would like to participate and provide study information as needed. Appointments are made directly at the HBOC-centre or via telephone.**Observations**In order to document changes in working practice as a result of dVP_FAM, observations of the screening process will be carried out. Approximately 6 months after the introduction of the digital care platform, a total of *N* = 16 observations will be conducted in study centres under interventions and control conditions and in the HBOC-centres. The participating study centres are visited and the medical staff are asked to simulate and explain their everyday screening and communication processes step by step. The observations focus on a comparison of the day-to-day processes with and without the care platform in more detail than is possible with the interviews described above alone.

### Sample size {14}

The primary endpoint for sample size planning is the percentage of women who had not been diagnosed with breast or ovarian cancer upon admission to the HBOC-centre. Both the control and intervention arms will recruit 22 gynaecological study centres. It is assumed that each study centre will include an average of *m* = 20 participants with familial cancer risk in 12 months. Under the intervention condition, it is expected that 70% of participants will not present with a diagnosis of breast or ovarian cancer when they visit the HBOC-centre. In contrast, under the control condition, only 60% are expected to be cancer-free [30]. To detect this difference at a two-sided significance level of* α* = 0.05 and a power of approximately 80%, at least *k* = 20 study centres with an average of *m* = 20 participants each must be randomised to each study arm. Therefore, a total of *k* = 40 study centres and 800 participants will be recruited. Assuming a dropout rate of about 10%, 22 study centres will be included in each study arm.

This calculation is based on an assumed intraclass correlation coefficient of ρC = 0.01. The sample size calculation was performed using the software PASS 16.0.4 (Test for Two Proportions in a Cluster-Randomised Design) Using the ‘Z-Test (Unpooled)’ method. No additional sample size calculation was conducted for the secondary endpoints.

### Recruitment {15}

#### Recruitment of study centres

The 40 study centres include primary care gynaecologists, breast and gynaecological cancer centres in Berlin, Brandenburg, and Mecklenburg-Vorpommern. Around 300 potential study centres will be informed about the project by e-mail. In addition, conferences and training courses will be used to address physicians personally. Other recruitment criteria include the size of the study centres and different degrees of urbanisation.

#### Recruitment of study participants (longitudinal study)

Participants in the study are recruited through the HBOC-centres after receiving specialist counselling. All patients seeking counselling who meet the inclusion criteria for the study are offered participation.

## Assignment of interventions: allocation

### Sequence generation {16a}

To counteract a potential imbalance of study centres in terms of type and size between the CGs and IGs, cluster randomisation will be performed according to the following stratification factors:▪ Type: primary care gynaecologists or breast cancer centres or gynaecological cancer centres▪ Size of primary care gynaecologists: < 1110 billing slips per quarter OR ≥ 1110 billing slips per quarter▪ Size breast cancer centres or gynaecological cancer centres: < 50 patients per year OR ≥ 50 patients per quarter.

The cut-off values for defining the different clusters are based on historical data of billing slips and patient numbers provided by the participating centres. We used the median of these reported values as the cut-off point to achieve approximately equal-sized clusters.

### Concealment mechanism {16b}

For the randomisation of the participating study centres, a randomisation list was created for each stratum using the R software (version 4.1.2, RStudio 2022.07.1) [31] and the R program package blockrand (version 1.5). In order to achieve a balanced distribution of study centres in the intervention and control conditions within the strata, a permuted block randomisation with flexible block lengths was used.

### Implementation {16c}

The randomisation of the study centres was carried out by the iBikE of Charité. The final randomisation list was then sent to the responsible research team, who then contacted the study centres via telephone/e-mail.

## Assignment of interventions: blinding

### Who will be blinded {17a}

As the intervention condition is visible, blinding of study centres is not possible in this setting. All statistical analyses are planned and documented in a statistical analysis plan (SAP), which is completed before the database is locked, ensuring that no data-driven choices in the analysis methods are made. Data analysis is completely independent of data collection. However, full blinding is not feasible in this case because the classification into the intention-to-treat (ITT) and per-protocol (PP) populations is directly linked to the treatment arm. Since the control group follows standard care, and the intervention group involves a digital tool that requires active engagement, protocol violations are more likely to occur in the treatment arm, with no protocol violations expected in the control arm. As a result, the ITT/PP distinction may reveal group assignment. If necessary, sensitivity analyses will be conducted to evaluate the potential impact of any bias.

### Procedure for unblinding if needed {17b}

This trial is unblinded.

## Data collection and management

### Plans for assessment and collection of outcomes {18a}

The database has been set up by Charité and is hosted on the Charité servers. The data to be collected during the study are primarily socio-demographic parameters and questionnaires. The data is collected directly via the Research Electronic Data Capture© (REDCap©) web application and is accessible only to study staff. The individual items comprising the questionnaire are entered into a data set. To obviate the possibility of data loss, the data set is saved with each entry. The data are stored in an encrypted format via REDCap©.

### Plans to promote participant retention and complete follow-up {18b}

Participants who have not returned the questionnaires on time will receive up to three reminders asking them to return the questionnaires within 1 week. Study staff will contact those who still do not respond again via telephone to encourage participation.

### Data management {19}

During the process of data entry and transfer, automated queries are pre-implemented to ensure the validity of the entered data. Upon conclusion of the study, the data are exported from the REDCap© database, processed for statistical analyses, and then imported into the R analysis software. The statistical analyses are conducted subsequent to the completion of data collection at the iBikE of Charité, utilising the R software in version 4.1.2.

### Confidentiality {27}

Data protection is a particularly sensitive issue when processing personal data of individuals with a family history of cancer. For this reason, specific data protection concepts were developed for the proposed research project. Data processing in the context of this study is subject to the General Data Protection Regulation (GDPR) and the Berlin Data Protection Act. Data will only be collected if study participants have agreed to the data collection and processing by signing the attached consent form (see Art. 6 para. 1a and Art. 9 para. 2a GDPR). All data will be collected exclusively for the purpose of the study described above and will be treated confidentially at all times. The data will be stored in encrypted form on a Charité server. Only the study staff of the research project have access to the encrypted data on this server. All employees are bound to confidentiality.

Re-identification lists are stored in a lockable cabinet in the study centres. Signed consent forms remain in the study centres. There is no physical connection between the study server (REDCap© database)—where the contents and progress of the consultation are stored—and the server of the HBOC-centre, where the re-identification list is stored. Questionnaires are created and managed via the REDCap© web application and are only accessible to study staff. Audio files, transcripts of the interviews as well as the observations are stored internally on Charité computers. They are only accessible to study staff.

### Plans for collection, laboratory evaluation and storage of biological specimens for genetic or molecular analysis in this trial/future use {33}

No biological specimen will be collected.

## Statistical methods

### Statistical methods for primary and secondary outcomes {20a}

All statistical analyses will be planned and documented in a SAP, which will be finalised prior to the database closure. The final analyses are carried out using the software R (version 4.1.1) and RStudio IDE (version 2022.07.1).

The analyses include both the per-protocol and the intention-to-treat populations. The per-protocol population consists of all study participants who have completed the study in the study arm initially planned by cluster randomisation and for whom all data for the planned analyses are available at different study time points (*t*0, *t*1, *t*2). The intention-to-treat population consists of all study participants based on the initial study arm allocation determined by cluster randomisation, irrespective of the study arm in which the study participants actually completed the study.

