### Trial design {8}

The trial is designed as a two-arm multicentre, cluster-randomised mixed-methods study. The convergent design is used as the mixed-method design method. The mixed-methods approach combines qualitative and quantitative methods in a single research design [16]. In this way, the weaknesses of the two methodological approaches (quantitative and qualitative) can be balanced out. The design of our study is intended to quantify the effect of the dVP_FAM compared to standard care and at the same time to provide a deeper understanding of the effects of the digital intervention on the everyday practice of patients and health care providers. The quantitative methods should meet the requirements of theory- and hypothesis-driven research as well as the statistical generalisability of findings [16], which requires the recruitment of a large sample. In addition, we use a qualitative approach, which is intended to capture more in-depth patterns [16]. The qualitative part is more open-ended and less hypothesis-driven than the quantitative part. Individual cases will be described in as much detail as possible. Both approaches thus form a field of tension between standardisation and methodological openness and flexibility. In our project, the methodology is complementary in order to obtain a comprehensive picture of the primary and secondary endpoints. The intervention starts at the primary gynaecological care level by screening for familial risk of breast and/or ovarian cancer using the digital platform in the intervention arm. If a patient meets the inclusion criteria for a familial risk of breast and/or ovarian cancer, the physicians in the study centre can recommend an appointment for specialised care and counselling in a HBOC-centre via the digital platform. In the control arm, referrals will be made according to standard practice. The primary endpoint is the quantitative one-time assessment of the proportion of individuals with a family history of cancer who are not diagnosed with cancer when presenting at specialised counselling compared to those with a family history of cancer already diagnosed with cancer. It is assumed that the treatment group demonstrates superiority over the control group. All women who are assessed for the primary endpoint are additionally asked whether they would like to participate in the longitudinal study. The secondary endpoints, transsectoral information exchange, care efficiency, quality of life and patient empowerment, are assessed as follows: (1) a longitudinal study will be conducted at three measurement points (baseline, after 3 months, after 9 months), (2) semi-structured interviews with patients, physicians and medical assistants, and (3) field observations. In addition, a multidisciplinary team will analyse the ethical, legal and psychosocial (ELSI) implications of the development and use of the dVP_FAM throughout the project.

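### The one per-protocol definition ties the primary endpoint, recorded once at counselling, to complete t0–t2 questionnaires, and conflicts with the blinding section on what per-protocol means

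*Protocol article*

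**What the plan says.** **Analysis sets.** Statistical methods for primary and secondary outcomes {20a} states: "The analyses include both the per-protocol and the intention-to-treat populations". Per-protocol means "all study participants who have completed the study in the study arm initially planned by cluster randomisation". A second condition limits the set further, to those "for whom all data for the planned analyses are available at different study time points"; the sentence names these points as t0, t1 and t2. No separate rule is given for the primary endpoint. For the other set: "The intention-to-treat population consists of all study participants based on the initial study arm allocation determined by cluster randomisation". The subsection on the primary endpoint analysis fixes the model, the Wald test and the 5% level without naming a set.

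**Primary endpoint.** Trial design {8} says: "The primary endpoint is the quantitative one-time assessment of the proportion of individuals with a family history of cancer". Outcomes {12} places it after counselling at the HBOC-centre. Table 1 marks it at t0 only, with monitoring, not a questionnaire, as its source. Trial design {8} adds that women assessed for this endpoint are then also invited into the longitudinal study. Participant timeline {13} describes the H1 population: "Patients with familial cancer risk according to the DKG-checklist are included in the analysis of the primary endpoint". It also says that the t0 questionnaire is e-mailed after counselling and that t1 and t2 follow at 3 and 9 months.

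**Meaning of a violation.** Who will be blinded {17a} links the split between the sets to active use of the digital tool and says that "protocol violations are more likely to occur in the treatment arm, with no protocol violations expected in the control arm".

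**Consent.** Confidentiality {27}: "Data will only be collected if study participants have agreed to the data collection and processing by signing the attached consent form".

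**The concern.** A per-protocol set normally isolates people treated as planned. Here, membership also depends on returning questionnaires up to nine months after the H1 outcome has been fixed. Joining the longitudinal study is voluntary, and its own criteria exclude, among others, women in severe psychological distress. Women who decline, are ineligible or skip a wave leave the per-protocol analysis of H1 although their outcome is known.

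Three things are at stake.

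- **Precision.** The sample size section applies its 10% dropout to centres. Nothing covers the loss of individual patients.
- **Bias.** Completion could plausibly depend on cancer status. It could depend on it differently by arm, since intervention patients already use a digital platform.
- **Consistency.** {17a} and {20a} describe different per-protocol sets under one name.

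**Working it through.** **1. The passages side by side**

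| Question | {8}, {12}, {13} | {17a} | {20a}, per-protocol |
|---|---|---|---|
| When is the H1 outcome known? | At counselling, once | – | Data required through t2 (9 months) |
| What removes a patient? | Not meeting the DKG checklist | Not using the platform as planned | Not completing in the allocated arm, or missing data at t0, t1 or t2 |
| Are controls removed? | – | None expected | Yes, any control with a missing wave |

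The last row is a direct conflict. A control patient who skips t2 has violated nothing under {17a} but is excluded under {20a}.

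**2. The plan's own power**

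Inputs from Sample size {14}: 70% versus 60% cancer-free, 20 centres per arm, m = 20 participants per centre, ICC 0.01, two-sided 5%, unpooled Z-test.

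- Design effect: 1 + (20 − 1) × 0.01 = 1.19
- Effective n per arm: 400 / 1.19 = 336
- Standard error: √[(0.7×0.3 + 0.6×0.4) / 336] = √(0.45 / 336) = 0.0366
- Power: Φ(0.10 / 0.0366 − 1.96) = 78.0%

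This agrees with the stated figure of approximately 80%. No sample-size number is disputed.

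**3. The same formula on the complete-data set**

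Let r be the share of H1 patients with complete t0–t2 data, that is, consent multiplied by completion. The documents give no value, so r is an assumption, taken as equal in both arms. Then m = 20r and the design effect is 1 + (20r − 1) × 0.01.

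| r | Per arm | Design effect | Power |
|---|---|---|---|
| 100% | 400 | 1.19 | 78.0% |
| 90% | 360 | 1.17 | 74.4% |
| 80% | 320 | 1.15 | 70.1% |
| 70% | 280 | 1.13 | 65.0% |
| 60% | 240 | 1.11 | 59.2% |
| 50% | 200 | 1.09 | 52.4% |

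For scale, 70% consent with 70% of those completing all waves gives r = 0.49, close to the last row.

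**4. Bias when there is no true effect**

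Suppose 60% are cancer-free in both arms. With completion a among cancer-free women and b among diagnosed women, the proportion observed in the set is 0.6a / (0.6a + 0.4b). All rates are assumed.

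If completion depends on status in the intervention arm only, the control arm stays at 60%:

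- a = 70%, b = 50%: 0.42 / 0.62 = 67.7%, a false difference of +7.7 points
- a = 80%, b = 60%: 0.48 / 0.72 = 66.7%, or +6.7 points
- a = 70%, b = 60%: 0.42 / 0.66 = 63.6%, or +3.6 points
- a = 60%, b = 70%: 0.36 / 0.64 = 56.25%, or −3.75 points

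If the same a and b hold in both arms, both show the same proportion (67.7% each in the first case) and the null bias is zero.

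**The case against.** The best defence is that the per-protocol wording can be read analysis by analysis: H1 needs only the t0 status record, so only that must be present. The reading is possible, but the sentence itself names all three time points, requires completion of the study and makes no exception for H1. The text therefore needs clarifying even on this reading.

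A reader might also infer stronger claims that the documents do not support.

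- **That the loss falls on one arm.** The {17a} sentence concerns platform engagement. The completeness condition applies to both arms.
- **That requiring complete data defeats the multiple imputation in {20c}.** Imputation remains fully usable in the intention-to-treat set, and pairing that with a complete-case per-protocol set is coherent.
- **That the intention-to-treat set contradicts the {13} population.** This holds only if *study participants* means women who consented to the longitudinal study. Recruitment {15} and Confidentiality {27} lean that way. Sample size {14}, however, uses the word participants for the 800 women of the primary endpoint, and {10} labels its patient criteria, written consent included, as belonging to the longitudinal study. The conflict with the per-protocol set does not need this reading.
- **That the answer to H1 could be picked after seeing the data.** The analysis plan is to be finished before database lock and may rank the sets. It is not shown, so the missing ranking is not in itself a fault.

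The bias figures are illustrations, and a reader could fairly choose milder ones.

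**Conclusion.** The concern holds in this form: {20a} states a per-protocol rule that is wrong for H1 and cannot be squared with {17a}. Followed as written, it removes women in both arms for reasons unrelated to the endpoint or to adherence.

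The power loss in that set depends wholly on the assumed completion rate and on equal loss in both arms. Bias requires completion to depend on cancer status differently by arm; its direction and size are unknown. The intention-to-treat analysis and the collected endpoint data are unaffected. This should be fixed, but it does not undermine the design.

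**What to change.** Changes to {20a}, with matching edits elsewhere:

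1. State that H1 is tested in the intention-to-treat set: all patients referred by a randomised centre who meet the DKG checklist at counselling (the {13} population), analysed by the centre's allocated arm, whether or not they join the longitudinal study.
2. Remove the questionnaire-completeness condition for H1. Reconcile the per-protocol definition with the adherence concept in {17a}. Label any per-protocol analysis of H1 as sensitivity, and note that adherence exclusions will fall mainly in the intervention arm, so that this analysis carries its own selection.
3. Clarify in {27} whether the consent condition covers the status-only endpoint record.

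The cost is wording in the protocol and the analysis plan before database lock, plus an ethics clarification if the status-only record is not already covered. No new data are needed.
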